### Trial Design

The evaluation of the “*Support for Life*” complex intervention will occur within a step-wedge cluster Randomized Controlled Trial (cRCT) involving multiple community health centers across three states over 3 years. Clusters are the community health centers, and approximately 10 centers in each state will participate in this study. Half of the centers (Group A) will be randomized to receive the intervention in year 1 and the other half in year 2 (Group B).

This “*Support for Life*” complex intervention proposes to trial a framework of a single service, highly flexible holistic approach to support for people with dementia and their families/carers. It will provide a platform to integrate current services and health care, provide emotional support, and enhance community and social engagement. Important principles are
Protecting the person with dementia and their rights to full citizenship regardless of their age, gender, and cultural background.Providing access to support where there is diminished decision-making capacity, retaining respect for the person with dementia but also the advocating for the rights of the family and caring unit.Improving access to palliation and “end of life care” in the setting of advanced or impaired decision-making, including with those who live alone.

This type of response builds on the strengths in a caring unit and addresses the needs of individual relationships. In line with “codesign” and “consumer directed care” (CDC) principles, the person with dementia, their family, and other members of the caring unit will actively design/influence what this service response will look like. Ongoing evaluation will allow for flexibility and change.

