**Figure 1 F1:**
[figure not shown]
**“Support for Life” stepped wedge cluster randomized control trial (SWcRCT) study design**. Overall, there are 30 clusters participating, 10 clusters in each state, and so the above figure shows the design that is replicated in each state. In each cluster, we aim to recruit 10 study participants having dementia or cognitive impairment, making the overall recruitment target at 300 participants. Data are collected from all participants during the seven data collection time points shown by a dashed-line in the above figure (i.e., at baseline and 3, 6, 12, 15, 18, and 24 months). We expect an attrition rate of 20 percent; therefore, we expect approximately 240 participants with dementia or cognitive impairment and approximately 1,680 participant data points to be examined in this SWcRCT. Attrition is expected to occur at any time point, and the modeling will include all participant data; participant data may be complete (available from all seven time points) or incomplete (available from one to six time points). The intensive intervention phase is shown in dark blue. The post-intervention phase is shown in light-blue (this is the second year for the year 1 intervention group), where participants can still access the intervention, but the intervention will no longer be promoted at those clusters.

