### Missing Data

The analysis method chosen will use all available data. Every effort will be made to minimize missing outcome data at each wave, and reasons individuals are lost to follow-up will be recorded. A missing data analysis will seek to identify systematic patterns of missing data and identify instances where, despite the efforts of the research team, data may be missing not at random (MNAR). Whether or not data are identified as MNAR, for each primary outcome and other key variables with missing data, multiple imputation using multivariate regression with factors of age, gender, state, and time will produce 100 estimates for each missing item – supporting optimal statistical estimation. Sensitivity analyses will be conducted to assess the robustness of the missing data assumption made in the primary analysis. A detailed analysis plan will be developed for secondary and sensitivity analyses.

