## Outcomes

The primary outcome for the economic analysis is the quality adjusted life years (QALYs). Utility values will be derived from the CES, and EQ-5D-5L will be used to construct QALYs over 12 months using an area under the curve analysis. QALYs for both the carer and the participant will be combined for use in a cost–utility analysis. Research is currently underway to develop an algorithm for estimating utility values from the QOL-AD (CI [name]), and if an algorithm is available, QALYs will also be estimated from this instrument and compared with the values obtained from the generic EQ-5D-5L instrument.

Cost and QALYs will be combined into an Incremental Cost-effectiveness ratio (ICER). The analysis will be over 12 months to match the trial duration and will take a limited societal perspective in order to incorporate the costs and outcomes of the carers and participants as well as the health-care costs and outcomes. Uncertainty in the cost–utility results will be estimated using non-parametric bootstrapping techniques and represented as cost-effectiveness acceptability curves.

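### The imputation rule covers every missing primary score and does not separate scores that were not collected from scores that cannot exist because of death

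*Protocol article*

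**What the plan says.** The Missing Data section of the protocol article sets the rule without condition: "Whether or not data are identified as MNAR, for each primary outcome and other key variables with missing data, multiple imputation" is to be used. The imputation model is "multivariate regression with factors of age, gender, state, and time", and it "will produce 100 estimates for each missing item". The same section says that "reasons individuals are lost to follow-up will be recorded", but does not link those reasons to what is imputed. It promises sensitivity analyses on the missing-data assumption and adds: "A detailed analysis plan will be developed for secondary and sensitivity analyses".

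Both primary outcomes, QOL-AD for the person with dementia and CES for carers, are scheduled at seven visits from baseline to 24 months (Outcomes and Table 1). The legend of Figure 1 states: "We expect an attrition rate of 20 percent". It does not split this by cause, and it allows losses at any time point. Death is not mentioned in the article. The nearest reference is a principle listed under Trial Design, which begins "Improving access to palliation and" and goes on to end-of-life care. On the economic side, the article plans to "construct QALYs over 12 months using an area under the curve analysis".

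**The concern.** A score that was not collected and a score after death are different things. The first has a true value that imputation tries to recover. The second has none, and no choice of covariates makes a predicted value valid. The rule covers both, because nothing in it depends on why the item is absent. The four imputation factors do not include vital status, so a visit after death would be filled with a value typical of living participants of the same age, gender, state and time.

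Deaths are foreseeable here: the participants have memory problems, cognitive decline or dementia, follow-up lasts two years, and access to end-of-life care is one of the trial's principles. At stake is what the estimated difference means. An estimate from the completed data would describe a population in which nobody dies, without the article having chosen that. The same holds for CES once the person cared for has died. For QALYs, time after death should contribute nothing, so an imputed living utility there credits time that was not lived.

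**Working it through.** **Inputs from the article.** 30 clusters of 10, so 300 participants (Sample Size); 20% attrition (Sample Size and Figure 1 legend); visits at baseline, 3, 6, 12, 15, 18 and 24 months (Outcomes); QALYs over 12 months (economic Outcomes section).

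**The article's own figures first.** 300 × (1 − 0.20) = 240 participants, and 240 × 7 = 1,680 data points. Both match the Figure 1 legend exactly. The full grid is 300 × 7 = 2,100 scores per primary outcome, so these figures leave 2,100 − 1,680 = 420 unobserved, as if lost participants contributed nothing. The legend also says that incomplete participants are kept in the model, so the number to impute is smaller.

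**Scores to impute if all 60 losses (300 × 0.20) come after baseline.**
- Fewest, all missing month 24 only: 60 × 1 = 60.
- Most, all lost straight after baseline: 60 × 6 = 360.
- Losses spread evenly over the six follow-up visits: 60 × 3.5 = 210.

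**How many of these could fall after death.** The article gives no death rate. Assume that 25%, 50% or 75% of the 60 losses are deaths, that is 15, 30 or 45.

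With death times uniform over 24 months, the visit at month t is missed with probability t/24. The expected number of visits lost per death is (3 + 6 + 12 + 15 + 18 + 24)/24 = 78/24 = 3.25.

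| Share of losses that are deaths (assumed) | Deaths | QOL-AD scores after death, × 3.25 | Share of 2,100 | Scores if spread evenly over visits, × 3.5 | Share of 2,100 |
|---|---|---|---|---|---|
| 25% | 15 | 49 | 2.3% | 53 | 2.5% |
| 50% | 30 | 98 | 4.6% | 105 | 5.0% |
| 75% | 45 | 146 | 7.0% | 158 | 7.5% |

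The two ways of spreading deaths agree closely. With one carer per participant, the number of CES scores after the death of the person cared for would be about the same.

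**QALYs, only if the rule is applied to EQ-5D-5L.** At an assumed living utility of 0.6 and death on average halfway through the 12 months, each death in that period would be over-credited by 0.6 × 0.5 = 0.3 QALY.

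**What cannot be computed.** These are counts of affected scores. Turning them into a bias in the intervention effect would need death rates by group and the gap between imputed and appropriate values. The article gives neither, and for a score after death there is no appropriate value to compare with.

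**The case against.** The strongest reply is that the article never says a visit after death counts as missing. A score that cannot exist is ordinarily not a missing item, and handling of deaths is the kind of detail a condensed article leaves to a fuller document. Part of this stands: a later plan could exclude such visits. But the rule for the primary outcomes is not left open. Its trigger, scope, factors and number of imputations are all stated, and the later plan is promised only for secondary and sensitivity analyses. The objection is to a stated rule that is too broad, not to a missing detail. Sensitivity analyses on the missingness assumption would not repair it, because a score after death is not a matter of missingness mechanism.

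Other replies limit the point, and a reader should not go beyond them:

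- **That the primary estimates will contain invented scores.** This is not established. Primary Analyses specifies a mixed model without mentioning imputation, and the Figure 1 legend and the opening of Missing Data speak of using all available data. It is unclear which analysis gives the primary result. Relying on the mixed model alone would not settle the matter either, since it implicitly extrapolates past death.
- **That a mortality difference would be hidden.** Reasons for loss are recorded and patterns of missingness will be examined, so the information would exist.
- **That QALYs would be overstated.** This holds only if EQ-5D-5L is treated as one of the other key variables, which the article does not say. A 5-point difference in 12-month mortality would shift the incremental QALY by 0.05 × 0.3 = 0.015. With 15 deaths spread evenly over 24 months, only about 7.5 fall in the first 12, or 5% of one group of 150, so such a difference would need all of them in one group.
- **That CES is void whenever caring ends.** A carer may still answer it after residential placement, and family members are eligible in their own right. The argument covers only the death of the person cared for, and even there it is an inference from the same wording.
- **That many losses are deaths.** The article does not say so. Its recruitment quota puts half of each cluster under 65, its eligibility criteria admit people with memory problems only, and its limitations section links dropout to waiting for the intervention.

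**Conclusion.** The concern holds as a defect in the wording of a fixed rule. As written, the rule does not distinguish uncollected scores from scores after death, and applied literally it fills the latter with values predicted for the living. The size rests on one assumption that the article does not supply: if deaths make up 25% to 75% of the 60 expected losses, roughly 2% to 7% of the 2,100 scheduled QOL-AD scores are affected. The consequence for any estimate is conditional on that estimate using the imputed data, and the consequence for QALYs is conditional on the rule reaching EQ-5D-5L. No direction or size of bias in the QOL-AD or CES effect can be claimed. The point does not depend on the power calculation.

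**What to change.** In Missing Data, restrict multiple imputation to visits at which the participant was alive and, for CES, to visits at which the person cared for was alive. Report deaths by randomised group and wave. In the economic analysis, set utility to zero from the date of death when building QALYs. State how death enters the primary comparison. More than one estimand is defensible: a while-alive comparison, for example, is a reasonable choice, but it compares survivors, who may differ between groups if mortality does. The choice should therefore be made and justified rather than left implicit.

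Restricting the imputation needs only a change of analysis wording, since reasons for loss are already to be recorded; the QALY step also needs the date of death. Slightly fewer scores would enter the imputed analysis. Stating how death is handled in the primary comparison takes some thought, but no change to recruitment, visits or intervention.

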#### Qualitative Analysis

Interview transcripts and journal entries will be managed using QSR NVivo (Qualitative Solutions and Research, Melbourne, Victoria). Interview data will be initially coded into broad topic areas using content analysis, and then constant comparative method will be applied to develop theoretical insights.

#### Economic Analysis

##### Resource Use

The cost of the delivery of the program will be calculated using actual wage rates, and resources used for each participant subtracting any resources used specifically for the purposes of research. Health-care resource use will be costed for each participant using administrative data or data collected using the RUD instrument by multiplying use by appropriate unit costs sourced from government databases. These include Medicare for items such as GP and specialist visits, PBS for medications, and National Hospital Cost data reports for hospital and ED presentations. Community care will be costed using administrative data from the RDNS. Costs over 12 months will be compared between groups using a generalized linear model, which is able to account for the non-normal distribution of cost data. Cost of carer time will be accounted for using a proxy good method (17) to recognize the value of unpaid caregiving duties. Costs will be reported by sector (health, community, and type of participant) in order to understand the implications of the intervention to different interest groups and sectors.

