### Outcomes

**Primary outcomes** (baseline, 3, 6, 12, 15, 18, and 24 months)*Person with dementia*
Improvement in quality of life (suitable for use by people with moderate to severe levels of dementia) (QOL-AD) (7)*Carer/family members*
Improvement in well-bein*g* of carer/family unit [Carer experience scale (CES)] (8, 9)**Secondary outcomes** (baseline, 6, 12, 18, and 24 months)*Person with dementia*
Reduction in symptoms of depression (GDS 15) (10)Increased attendance at social activities/services (staff/family/carer report/interviews)Increased engagement in social activities/services/ability to continue to participate in regular activities (staff/family/carer report/interviews)Change in health-care service utilization [client records/resource utilization in dementia (RUD) (11) health records]Delay in accessing permanent residential aged care services (client records/interviews)*Carer/family members*
Reduction in carer depression/psychological distress [General Health Questionnaire-12 (GHQ-12)] (12)Increase in social engagement and ability to continue regular activities (self report/interviews).

(See Table 1 for a full list of instruments).

**Table 1 T1:** **Outcome measures**.

	Baseline	3 months	6 months	12 months	15 months	18 months	24 months

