## Economic Methodology and Analysis

Utility measured by EQ-5D-5L (13)Reduction in health service utilization measured by RUD and administrative dataReduced carer time (paid and unpaid) measured by RUDDelay in permanent admission to residential care.

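### The cost comparison and cost-utility bootstrap state no allowance for centre randomisation, and the EQ-5D-5L that the QALYs need has no scheduled time point and no settled relation to the CES

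*Protocol article*

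**What the plan says.** **Design and clinical analysis.** Trial Design states: "Clusters are the community health centers, and approximately 10 centers in each state will participate in this study". It goes on: "Half of the centers (Group A) will be randomized to receive the intervention in year 1", with the other half following in year 2. The Randomization section also allocates centres. Sample Size uses an ICC of 0.05 at centre level. Under Primary Analyses, continuous outcomes get a linear mixed model and binary outcomes a generalized linear mixed model, both with centre and individual as random effects.

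**Costs and uncertainty.** Resource Use states: "Costs over 12 months will be compared between groups using a generalized linear model". The only reason given is that cost data are not normally distributed. The economic Outcomes section says that uncertainty in the cost-utility results "will be estimated using non-parametric bootstrapping techniques and represented as cost-effectiveness acceptability curves". Neither place mentions centre.

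**Utilities.** Economic Methodology and Analysis lists "Utility measured by EQ-5D-5L" and no other utility source. The economic Outcomes section says: "Utility values will be derived from the CES, and EQ-5D-5L will be used to construct QALYs". This is done by area under the curve over 12 months, and carer and participant QALYs are combined.

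**Schedule.** The clinical Outcomes section refers the reader on: "See Table 1 for a full list of instruments". That table has rows for the QOL-AD, CES, GDS 15, RUD, GHQ-12 and interview or client-record items. It has no row for the EQ-5D-5L. Schedule of Events and the data collection section give times for primary and secondary measures only.

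**The concern.** The protocol uses mixed-model terms with centre effects for the clinical outcomes and a different term, without them, for costs. A generalized linear model handles skewed costs, but by itself it does nothing about people in the same centre being alike. The same is true of a bootstrap that resamples individuals. If both are run in their default form, the cost difference and the acceptability curve will look more precise than a centre-randomised comparison allows. Cost-effectiveness is one of the trial's headline aims.

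The utility problem is of another kind. An area-under-the-curve QALY needs dated measurements, including one at baseline. If the visit forms are built from Table 1 as it stands, the EQ-5D-5L could be left out, and a missed baseline utility cannot be recovered at analysis. Since two sections also describe the utility source differently, two analysts could build different ICER denominators from the same text.

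**Working it through.** **Inputs from the protocol.** There are 30 centres, 15 per group, with 10 participants/families each and 20% attrition, so 8 to 10 per centre (Sample Size, Figure 1 legend). The ICC is 0.05 and the significance level 0.05 (Sample Size), taken here as two-sided. Recruitment and Sequence Generation are worded as if individuals were allocated. Trial Design, Randomization and Sample Size make the centre the unit, and that is used here.

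**The plan's own figure.** The economic section states none. The nearest is the stated power of 0.80 for the clinical outcomes. A standard stepped-wedge variance was used, with period fixed effects, a centre random intercept, seven time points, 15 centres per sequence, and no added correlation between one person's repeated measures. It gives:

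- power 0.810 at effect size 0.25 with 8 per centre;
- power 0.822 at effect size 0.23 with 10 per centre, and 0.742 with 8.

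So 0.80 is reproduced at 0.25 after attrition, and at 0.23 only before attrition. This shows that the ICC of 0.05 and these centre sizes are consistent with the protocol's own calculation.

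**Clustering in the economic contrast.** Over 12 months, Group A versus Group B is a parallel comparison of randomised centres. With m people per centre and intraclass correlation ρ:

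- Design effect DE = 1 + (m − 1)ρ.
- Correct SE ÷ SE without centre = √DE, so the latter is too small by 1 − 1/√DE.
- Actual coverage of a nominal 95% interval = 2Φ(1.96/√DE) − 1. The type I error is one minus this.

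At ρ = 0.05:

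- m = 8: DE = 1 + 7 × 0.05 = 1.35; √DE = 1.162; SE too small by 1 − 1/1.162 = 14%; effective sample 240/1.35 = 178.
- m = 10: DE = 1 + 9 × 0.05 = 1.45; √DE = 1.204; SE too small by 1 − 1/1.204 = 17%; effective sample 300/1.45 = 207.

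The protocol gives no ICC for costs or QALYs, so a range is shown:

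| ICC (assumed) | DE, m = 8 / 10 | Coverage, m = 8 / 10 | Type I error, m = 8 / 10 |
|---|---|---|---|
| 0.01 | 1.07 / 1.09 | 94.2% / 94.0% | 5.8% / 6.1% |
| 0.02 | 1.14 / 1.18 | 93.4% / 92.9% | 6.6% / 7.1% |
| 0.05 | 1.35 / 1.45 | 90.8% / 89.6% | 9.2% / 10.4% |
| 0.10 | 1.70 / 1.90 | 86.7% / 84.5% | 13.3% / 15.5% |

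On the acceptability curve, a reported probability of 0.95 becomes Φ(1.645/√DE). At ICC 0.05 that is 0.922 (m = 8) or 0.914 (m = 10).

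These results are analytic, using a normal approximation and equal centre sizes. With near-equal centre sizes, the mean differences in cost and QALYs are unaffected.

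**EQ-5D-5L and CES, side by side.**

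- The RUD, the other economic instrument, has time points in Table 1. The EQ-5D-5L has none there or in either schedule section.
- One economic section names the EQ-5D-5L alone for utility; the other brings in the CES.
- Sample Size describes the CES as a score from 0 to 100 with SD 10. The economic section says that an algorithm is needed before the QOL-AD can give utilities, but states no conversion for the CES.

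**The case against.** The strongest reply is that the clustering point rests on silence. A generalized linear model can carry cluster-robust errors and a non-parametric bootstrap can resample centres, so the remedy is compatible with the wording. A condensed article may also leave such detail to a fuller plan. This stands in part. A reader might infer that the plan ignores clustering or treats participants as independent, but the text does not say so. What remains is that the protocol spells out centre effects for the clinical outcomes, then names another model class and justifies it by skewness alone. Run as named, the methods carry no allowance for centre.

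Four other stronger readings are not supported:

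- *The ICER would be wrong.* Clustering affects its uncertainty, not its point estimate. Only the unclear utility source could alter the estimate.
- *The EQ-5D-5L is unplanned.* It is named as the utility measure. The defect is a missing schedule entry.
- *CES and EQ-5D-5L values will be pooled in one denominator.* The sentence can also be read as CES values for carers with QALYs from the EQ-5D-5L. The later comparison of any QOL-AD-based QALYs with the EQ-5D-5L alone fits that reading. No rescaling of the CES is proposed, so no QALY size can be attached to it.
- *The 12-month horizon is an error.* The protocol says: "The analysis will be over 12 months to match the trial duration". Data collection runs to 24 months, so the reason is loosely worded. The horizon is defensible, because Group B gains access in year 2 and only year 1 has concurrent usual care. No result changes.

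**Conclusion.** The point holds as a moderate one about the precision of the economic results and about two gaps in their specification. If the economic methods are run as named, and if costs and QALYs share the ICC of 0.05, the intervals and acceptability curves are too certain by a material but not extreme amount, as sized above. At an ICC of 0.01 the effect is minor; at 0.10 it is serious. The ICC for costs is the main assumption, with two-sided testing and near-equal centre sizes alongside it.

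The missing EQ-5D-5L time points and the differing statements on the CES depend on no numerical assumption. They follow from comparing sections of the same article, and the schedule gap is the one that cannot be mended after data collection.

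**What to change.** 1. **Cost model.** State a generalized linear model with a centre random effect, or with cluster-robust errors (with a small-sample correction, as there are 30 centres), for the year-1 Group A versus Group B contrast.
2. **Bootstrap.** State that centres are resampled within group and that each family's costs and QALYs stay paired.
3. **Schedule.** Add the EQ-5D-5L to Table 1 and Schedule of Events at existing visits, including baseline and 12 months, and say who completes it (participant, proxy, carer).
4. **Utility source.** Reconcile the two economic sections. Use the EQ-5D-5L as the common QALY measure for participants and carers, and report CES-based values separately unless a conversion to a QALY-anchored scale is stated.
5. **Wording.** Describe the 12 months as the period with concurrent controls.

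The cost is some revised text, slightly wider intervals, and one short questionnaire at visits that already take place. The sample size does not change.
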